#### Randomization procedure

Patient enrolment is performed by the study data managers or physicians with a phone call to the local Research and Statistics Unit, which generated the allocation sequence: the responder simultaneously enters the patient and caller names and uses a predefined randomization list to make the assignment. Group allocation is revealed to researchers performing interventions and to patients after baseline evaluations (T0) are completed.

#### Blinding

This is an open-label study, due to the limited number of professionals involved in a single institution project.

#### Statistical analysis

Statistical analyses will be performed according to the intention-to-treat approach. Statistical techniques per study aims are as follows:
*Primary aim:* t-test for independent samples to compare the mean of the change (defined as T3 – T0 related date) in 6MWD between IG and CG. In case of heteroscedasticity, checked by folded F test, the Satterthwaite adjustment will be used.
*Secondary aims*:- t-test for independent samples to compare the mean of the change between IG and CG for 6MWD (T2 – T0 change), FEV1, FVC, DLCO and SF-12 score (T3 – T0 change), HADS score (T1 - T0 and T3 - T0), NRS score (T2 – T0 and T3 – T0) and LoS. In case of heteroscedasticity, checked by folded F test, the Satterthwaite adjustment will be used.- chi-square test to compare the proportion of postoperative complications between IG and CG;

Five percent significance will be used to assess the *p*-values and 95% two-sided confidence interval will be provided for each tested parameter; the confidence intervals will be calculated assuming normal distribution.

Statistical calculations will be performed by the local Research and Statistics Unit using SAS System release 9.2 or later, R release 3.3.3 or later, SPSS release 23 or later, according to the availability at the time of the data analysis.

Patient adherence to protocol may be a crucial issue in determining the efficacy of rehabilitation programmes, including exercise training. Although it has not been plainly demonstrated, in principle, non-attendance could affect exercise dose and influence the outcome of treatment [34]. Therefore, if patient compliance, is less than 80% [25], we will proceed with a second per-protocol analysis.

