##### 1.2.1.1.Primary outcome measure

The primary outcome measure to assess the superiority of intensive PR over standard care (SC) is the change in distance walked in six minutes (6MWD) measured six months after surgery, compared to baseline.

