### Measurements

Patients included in the study are assessed at baseline (T0), the day before surgery (T1), one month after surgery (T2) and six months after surgery (T3) [Table 2].

**Table 2 Tab2:** Assessments

	T0 Baseline	Randomization	T1 1 day before surgery (14÷21 days from baseline)		T2 (1 month ± 5 days after surgery)		T3 (6 months ± 5 days after surgery)	
			IG	CG	IG	CG	IG	CG
Pulmonary function (PFTs)	x		x				x	x
Exercise capacity (6MWT)	x				x	x	x	x
Quality of life (SF-12)	x						x	x
Mood disturbances (HADS)	x	Randomization	x	x			x	x
Pain (NRS)	x				x	x	x	x
Length of stay					x	x		
Postoperative complications					x	x	x	x

*IG* Intervention Group, *CG* Control Group, *PFTs* Pulmonary Function Tests, *6MWT* Six-Minute Walk Test, *SF-12* Short form 12, *HADS* Hospital Anxiety and Depression Scale, *NRS* Numeric Rating Scale

Baseline assessments are carried out immediately before randomization (T0) and include lung function, exercise capacity, QoL, mood disturbances and pain.

Static and dynamic respiratory volumes and DLCO are measured with full pulmonary function tests (PFTs). Exercise capacity is evaluated with 6MWT, according to current guidelines [11, 26]. Data on QoL are assessed with SF-12 [27], mood disturbances are evaluated using the HADS [28] and pain is quantified using the NRS [29].

The day before surgery (T1), all patients are re-assessed for mood disturbances. PFTs are repeated in the IG; treatment-related side effects and patient adherence to the intensive preoperative PR are also recorded.

One month after surgery (T2), patients repeat exercise capacity and pain evaluation using the same tools employed at baseline (T0). Data regarding LoS, postoperative complications and 30-day mortality are also recorded at this stage. Postoperative complication categories include acute respiratory failure, cardiac failure (including myocardial infarction), surgical site infection (including pneumonia and bronco-pleural fistula), arrhythmias (including atrial fibrillation), thrombosis and pulmonary embolism, neurological impairment (including stroke) and other (specified).

Long-term follow-up takes place 6 months after surgery (T3) and includes the assessment of lung function, exercise capacity, QoL, mood disturbances, pain and late postoperative complications. In the IG, patient adherence to the intensive postoperative PR and side effects are also recorded at 6 months.

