### Statistical considerations

#### Sample size

Since data for mean and standard deviations of 6MWT after lung surgery with or without treatment have never been published, Cohen’s medium effect size (d = 0.5) has been used to compute sample size based on the minimal significant variation reported (25 m) [33].

We also expect a potential dropout rate of about 10% for the aforementioned reasons. Thus, assuming 5% type I error and 80% power for this study, we plan to enrol 140 patients (about 70 patients in each arm).

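### The unadjusted t-test on change in 6MWD is a valid primary analysis, but adjusting for baseline 6MWD would be at least as precise (in large samples) and needs no new data

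*Protocol article*

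**What the plan says.** The Primary outcome measure section defines the outcome as "the change in distance walked in six minutes (6MWD) measured six months after surgery, compared to baseline". The Statistical analysis section then names the test for the primary aim: a "t-test for independent samples to compare the mean of the change (defined as" T3 minus T0), comparing the two arms. The only modification offered concerns unequal variances: "In case of heteroscedasticity, checked by folded F test, the Satterthwaite adjustment will be used". No covariate is named. The secondary change scores (6MWD at T2, FEV1, FVC, DLCO, SF-12, HADS and NRS) are treated in the same way.

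According to the Measurements section and its Table 2, 6MWD is taken at T0, immediately before randomization, and again in both arms at T2 (one month after surgery) and T3 (six months). T2 6MWD enters the analysis only as a secondary outcome.

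The Sample size section states that "Cohen’s medium effect size (d = 0.5) has been used to compute sample size", tied to a difference of 25 m, with 5% type I error, 80% power and about 10% dropout, giving 140 patients. It gives no correlation between baseline and follow-up.

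**The concern.** Subtracting the baseline is the same as regressing T3 on T0 with the slope held at 1. The real slope is usually below 1. When it is, the change score carries more residual variance than necessary, and a chance difference in baseline 6MWD between arms passes partly into the treatment contrast. A model that estimates the slope avoids both.

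This matters here because the sample size has no slack, and the Discussion itself warns that withdrawals after randomization may exceed the planned rate because of nodal disease found at surgery. Precision that can be had from data already collected would offset some of that loss.

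The article names the primary test outright. An analysis plan could not make an adjusted model primary without departing from it, so this is not a detail simply left to a document that is not shown.

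**Working it through.** **Inputs.** From the article: difference 25 m, d = 0.5, two-sided 5% (sidedness taken from the confidence intervals), 80% power, 10% dropout, 1:1 allocation, 140 enrolled. Implied: SD = 25/0.5 = 50 m; the article does not say whether this is the SD of the change or of 6MWD itself. Assumed, because not in the article: r, the T0–T3 correlation of 6MWD, and L = SD at T3 / SD at T0.

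**The plan's own figure.** n per arm = 2(1.960 + 0.842)²/0.5² = 62.8, so 63. The total is 126, and 126/0.9 = 140, which reproduces the stated number. With 63 per arm the exact (noncentral t) power is 79.5%; the normal approximation gives 80.1%.

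**Variance ratio.** With the T0 SD set to 1:

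- variance of the change = 1 + L² − 2rL
- residual variance after regression on T0 = L²(1 − r²)
- ratio = L²(1 − r²)/(1 + L² − 2rL)

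Denominator minus numerator is 1 − 2rL + r²L² = (1 − rL)², which cannot be negative, so the ratio is never above 1. It equals 1 only when the slope rL is exactly 1. With equal SDs (L = 1) it reduces to (1 + r)/2.

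**Power, assuming SD of change = 50 m and L = 1** (noncentral t; the degree of freedom spent on the covariate makes no visible difference). The second power column takes 20% loss, 0.8 × 70 = 56 per arm.

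| Analysis | Variance ratio | 63 per arm | 56 per arm |
|---|---|---|---|
| t-test on change | 1 | 79.5% | 74.6% |
| ANCOVA, r = 0.5 | 0.75 | 89.5% | 85.7% |
| ANCOVA, r = 0.6 | 0.80 | 87.6% | 83.5% |
| ANCOVA, r = 0.7 | 0.85 | 85.5% | 81.2% |
| ANCOVA, r = 0.8 | 0.90 | 83.5% | 78.9% |
| ANCOVA, r = 0.9 | 0.95 | 81.5% | 76.8% |

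**Unequal SDs.**

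- L = 1.2, r = 0.8: ratio = 1.44 × 0.36/(1 + 1.44 − 1.92) = 0.518/0.52 = 0.997. The gain almost vanishes (79.5% to 79.6% at 63 per arm).
- L = 0.8, r = 0.8: ratio = 0.64 × 0.36/(1 + 0.64 − 1.28) = 0.230/0.36 = 0.64. The gain is larger than in the table.

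**If 50 m is the SD of 6MWD itself** (equal SDs, normal approximation, 63 per arm), power for change score against ANCOVA is 66.0% against 83.7% (r = 0.3), 80.1% against 90.0% (r = 0.5) and 95.2% against 97.6% (r = 0.7).

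**Chance baseline imbalance.** The change-score and ANCOVA contrasts differ by (1 − r) times the baseline difference between arms when L = 1. One standard error of that difference is s√(2/63), with s = 50/√(2(1 − r)).

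- r = 0.5: s = 50.0 m, standard error 8.9 m, shift 4.5 m
- r = 0.8: s = 79.1 m, standard error 14.1 m, shift 2.8 m

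These compare with a target of 25 m.

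**T2 6MWD.** A simulation used 140 patients, 4,000 replicates, equal SDs, all pairwise correlations equal to r, a true effect of 12.5 m at T2 and 25 m at T3, and T3 values deleted at random. At r = 0.7 the standard error of the T3 contrast was:

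| T3 missing | ANCOVA on T0 | Likelihood model with T2 and T3 as outcomes |
|---|---|---|
| 0% | 7.86 | 7.86 |
| 10% | 8.21 | 8.14 |
| 20% | 8.87 | 8.75 |

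The repeated-outcome model therefore gains about 1% in standard error. Entering T2 as a covariate instead pulled the estimate from 25 m to about 20 m, because T2 already contains part of the effect.

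**The case against.** The best defence is that nothing is wrong. The t-test on change is unbiased over randomization, keeps its type I error, allows for unequal variances, matches the declared outcome and fits the calculation that gave 140. Under its own assumptions the plan has its stated 80%. All of this stands.

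Four stronger readings are tempting, and the article does not support them.

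- *That the baseline is wasted.* The change score uses every T0 value; only the gap between a slope of 1 and the true slope is lost.
- *That T2 6MWD is wasted.* It is a prespecified secondary outcome and adds little precision to the T3 contrast. Patients withdrawn for adjuvant treatment after surgery may have no T2 value either.
- *That patients without T3 are discarded.* The article states intention to treat and says nothing about missing values, which an article commonly leaves to a fuller document. The same applies to its silence on stratification.
- *That a gain of 10 points is available.* That is the r = 0.5 end of an assumed range, and it also needs equal SDs. Lung resection and a multi-component programme lie between T0 and T3, so equal SDs cannot be taken for granted.

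Timing also counts. Enrolment began in 2015, the trial is open-label, and the study physiotherapists collect the 6MWT. A late change to the primary analysis is credible only if it is documented and made blind to outcomes by arm.

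**Conclusion.** The point holds as an efficiency improvement. The article fixes an unadjusted analysis although a pre-randomization measurement of the same variable exists for use as a covariate. In large samples adjustment cannot lose precision at 1:1 allocation, and it removes the effect of chance baseline imbalance.

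The benefit is roughly 2 to 10 power points for r from 0.9 down to 0.5, given an SD of change of 50 m, equal SDs at T0 and T3, and 63 evaluable patients per arm. It can be near zero if the T3 SD exceeds the T0 SD. At 20% loss, and on the same assumptions, adjustment would keep power above 80% for r up to about 0.7. None of r, L or the meaning of the 50 m is in the article, so no single figure should be quoted. The planned test remains valid.

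**What to change.** By a documented amendment, before database lock and without sight of outcome data by arm:

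- Make the primary analysis a linear model of T3 6MWD on arm and T0 6MWD, with heteroscedasticity-robust standard errors. Modelling the T3 − T0 change with T0 as covariate gives the same arm effect, so the declared outcome need not change.
- Keep the t-test on change as a sensitivity analysis.
- Use the same form for the secondary change scores (6MWD at T2, FEV1, FVC, DLCO, SF-12, HADS, NRS). Length of stay, listed with them, has no baseline value and is not affected.
- Do not enter T2 6MWD as a covariate. Optionally, fit a mixed model with T2 and T3 as repeated outcomes, T0 as covariate and arm-by-visit terms, and take the T3 contrast. Its main use is to keep patients with T2 but no T3 in the analysis under a missing-at-random assumption.

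The cost is one paragraph of analysis wording, the amendment record and one degree of freedom. No new data and no change in sample size are needed.

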The definition of the best PR treatment programme required a careful review of the current literature [23], resulting in the definition of the following key elements:The inclusion of both aerobic and strength training of lower and upper limb muscles [2, 11, 35];The combination of outpatient and home-based treatment sessions. This should facilitate the enrolment of patients referred from provincial hospitals and might increase their compliance, minimizing the risk of attrition bias;The inclusion of inspiratory muscle training, incentive spirometry, airway clearance techniques and/or respiratory exercises, as lung cancer leads to respiratory impairment and COPD is a frequent comorbidity in patients affected by lung cancer [19, 20, 36, 37];The inclusion of group exercise training sessions during the postoperative phase, alongside individual guided and monitored home-based training, to facilitate mutual support among patients with NSCLC, whose vulnerable psychosocial condition could affect postoperative functioning and QoL [38]. In fact, a recent systematic review examining the spectrum of health care needs among people with lung cancer showed that psychological, emotional and social needs were most frequently specified and lack of acknowledgement of patients’ status by others were perceived as important issues [39]. Therefore, group sessions may facilitate the sharing of feelings, experiences and concerns, and may support patients in coping with their illness;The inclusion of scar massage in the postoperative phase to relieve tissue tension and reduce pain. In our clinical experience, patients frequently report pain and hypersensitivity around surgical scar.

At the time of planning this protocol, we estimated an overall 10% withdrawal rate, mainly due to perioperative morbidity and mortality, as well as unforeseen N1/N2 lymph nodal involvement diagnosed after surgery and requiring adjuvant therapies. However, more recent literature suggests a greater incidence of intraoperative lymph nodal upstaging [40] and even when an accurate staging workup is performed, including PET/CT and EBUS-TBNA when appropriate, minimal involvement of hilar nodes (N1 stage) remains difficult to assess preoperatively. Furthermore, more aggressive protocols are recommended by international guidelines in treating N1 NSCLC [41]. A greater than expected number of patients may therefore withdraw post randomization to ensure they receive the best cancer care.

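### A variance pre-test chooses the primary t-test; if arm sizes and SDs both differ, the error rate drifts slightly from 5%, and always using Satterthwaite removes the drift almost free

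*Protocol article*

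**What the plan says.** The primary analysis (protocol article, Statistical analysis, primary aim) is a "t-test for independent samples to compare the mean of the change (defined as T3 – T0 related date) in 6MWD between IG and CG". The next sentence gives the rule for unequal variances: "In case of heteroscedasticity, checked by folded F test, the Satterthwaite adjustment will be used". The same rule is repeated for the continuous secondary outcomes compared by t-test.

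For error control the section says "Five percent significance will be used to assess the" p-values, and that a "95% two-sided confidence interval will be provided for each tested parameter". No separate level is given for the folded F test.

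The Sample size section works from "assuming 5% type I error and 80% power for this study" and a "medium effect size (d = 0.5) has been used to compute sample size". It expects about 10% dropout and plans 140 patients, about 70 per arm, allocated 1:1.

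**The concern.** The rule has two stages. If the folded F test is not significant, the pooled t-test stands; if it is, the Satterthwaite version replaces it. A pre-test of this kind is weakest where it is most needed. At 63 v 63 it detects an SD ratio of 1.25 in only 41% of trials, and a ratio of 1.5 in 89%. A false assumption of equal variances is therefore often kept.

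That matters only if the arms also differ in size. If the smaller arm has the larger SD, the pooled standard error is too small, so the test rejects too often and the interval is too narrow. If the larger arm has the larger SD, both errors reverse. At stake is whether the nominal 5% and 95% of the primary superiority comparison are exact.

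Such a pattern is conceivable here. Only the intervention arm receives the 53-session programme, and the article accepts that "non-attendance could affect exercise dose and influence the outcome of treatment", which might widen the spread in that arm. It also warns: "A greater than expected number of patients may therefore withdraw post randomization to ensure they receive the best cancer care". The Sample size section says that no SDs have been published for this setting, so equality of variances cannot be checked in advance.

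**Working it through.** **1. The plan's own figure.** A difference of 25 m at d = 0.5 implies SD = 25 / 0.5 = 50 m. Per arm, n = 2(1.960 + 0.842)² / 0.5² = 2 × 7.85 / 0.25 = 62.8, so 63. With 10% dropout, 63 / 0.9 = 70 per arm, 140 in total. This matches the article, and 63 v 63 is the planned analysis set.

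**2. Why both conditions are needed.** The two versions use

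- pooled: SE² = s_p²(1/n₁ + 1/n₂), with s_p² = [(n₁−1)s₁² + (n₂−1)s₂²] / (n₁+n₂−2);
- Satterthwaite: SE² = s₁²/n₁ + s₂²/n₂, with approximate degrees of freedom.

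If n₁ = n₂ the two standard errors are identical and only the degrees of freedom differ. If the SDs are equal (normal data), the pooled test is exact. So neither condition alone does harm.

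**3. One case by hand (assumed 45 v 63, SD ratio 1.25, larger SD in the smaller arm).** Set the SDs at 1.25 and 1.

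- Expected pooled variance: (44 × 1.5625 + 62 × 1) / 106 = 1.2335.
- Pooled SE²: 1.2335 × (1/45 + 1/63) = 0.0470.
- True SE²: 1.5625/45 + 1/63 = 0.0506.
- SE ratio: √(0.0470/0.0506) = 0.964. The effective critical value is about 1.96 × 0.964 = 1.89, a two-sided error of about 5.9%. Simulation of the pooled test gives 5.86%.

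In this case the F test is significant in 36.3% of trials. In the other 63.7% the pooled test is kept, with a conditional error of 6.11%. That contributes 0.637 × 6.11% = 3.89 points to the overall 5.37%. The pre-test removes part of the excess error, but not all of it.

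**4. Simulated type I error.** Normal data, 400,000 trials per cell, F test at an assumed 5%. The simulation standard error is √(0.05 × 0.95 / 400,000) = 0.03 points. Retained numbers and SD ratios are assumptions. The entries for the planned rule are the worst case over SD ratios 1.15 to 2:

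| Retained per arm | Larger SD in smaller arm | Larger SD in larger arm |
|---|---|---|
| 58 v 68 | 5.2% | 4.9% |
| 56 v 70 | 5.2% | 4.8% |
| 50 v 63 | 5.3% | 4.7% |
| 45 v 63 | 5.4% | 4.6% |
| 40 v 63 | 5.5% | 4.5% |
| 35 v 70 | 5.8% | 4.3% |

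Further cells:

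- Equal arms (70/70, 63/63, 35/35), any SD ratio from 1 to 2: 4.9% to 5.1%.
- Equal SDs, unequal arms (58/68 to 35/70): 5.0% to 5.1%.
- 55 v 63, ratio 1.3, larger SD in the smaller arm: 5.13%.
- 35 v 63, ratio 1.4, same pattern: 5.6% to 5.8% across separate runs.
- Satterthwaite in every case: 4.9% to 5.1% throughout.

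Interval coverage is the complement: 100 − 5.8 = 94.2% to 100 − 4.3 = 95.7% at the extremes. At 45 v 63 the error peaks near a ratio of 1.25 and falls at larger ratios (5.16% at 1.5, 4.95% at 2), because the F test then nearly always detects the difference.

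**5. Heavy tails.** With equal SDs and t errors on 5 df at 45 v 63, the F test is significant in about 19% to 20% of trials instead of 5%. The t-test error is 4.91% under either rule.

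**6. Cost of the alternative.** Power for 25 m with SD 50 m in both arms, Satterthwaite always v planned rule: 63/63, 79.5% v 79.5%; 56/70, 79.0% v 79.0%; 50/63, 74.4% v 74.5%; 40/63, 68.6% v 68.8%.

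**The case against.** The strongest reply is that nothing is broken. The protocol foresees unequal variances, prespecifies the check and names the remedy. With the near-equal arms that 1:1 allocation plans, the rule holds 5% whatever the SD ratio. The article does not say that losses will differ by arm: the causes it names are perioperative morbidity and mortality, and nodal disease found at surgery that needs adjuvant therapy, and none of these is presented as related to arm. It says that non-attendance may affect outcome, not that it widens the SD. The largest errors need half of one arm to be lost, and attrition bias would then be the greater worry. All of this stands, and it limits the point to a small one.

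A reader might infer that unequal loss by itself invalidates the 5% level and the 95% interval. It does not: with equal SDs the rule gives 5.0% to 5.1% even at 35 v 70. A reader might also infer that the F test's sensitivity to heavy tails distorts the primary test. It affects which version is reported, but not the error rate; a false alarm merely selects the Satterthwaite version.

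What the reply does not remove is that the pre-test gains almost nothing. The alternative holds its level in every case examined, at a power cost of at most about 0.2 points.

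**Conclusion.** The point holds as a minor one. The stated rule does not guarantee exactly 5% when retained arm sizes and SDs both differ. The departure is about 0 to 0.3 points for modest imbalance and up to about 0.8 points if one arm loses half its patients and has the larger SD. In the reverse pattern the rule is conservative by up to about 0.7 points. With equal arms or equal SDs it holds about 5%.

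These figures rest on normal data, an F test at 5%, and assumed retained numbers and SD ratios. The documents show neither unequal loss nor unequal SDs. The main conclusion of the trial is not threatened.

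**What to change.** In the Statistical analysis section, replace the conditional sentence, for the primary aim and for the other continuous outcomes tested by t-test, with wording such as:

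*The t-test with Satterthwaite degrees of freedom will be used in all cases, without a preliminary variance test, and the 95% confidence interval will be taken from the same test.*

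The cost is one sentence, to be changed before the data are analysed, and at most about 0.2 points of power. The planned 140 patients do not change, and no extra data are needed.
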